#### 3D radiological analyses (B, F)

Aside from clinical purposes and evaluating inclusion and exclusion criteria, MRI-arthrographies are also acquired to obtain 3D shape parameters of the humerus, scapula and subacromial space with the use of MRI segmentation techniques (Amira 5.3, Visage Imaging Inc., San Diego, CA, USA).

*Main 3D radiological outcome parameters*: 3D shape parameters for humerus, scapula and subacromial space.

#### 3D kinematics and changes in subacromial volume (E, F, G)

Range of Motion (RoM) and 3D motions of forearm, humerus and scapula with respect to the thorax will be recorded by means of an electromagnetic tracking system: 'Flock of Birds' (FoB, Ascension Technology Corp, Burlington, VT, USA) and custom made computer software (FOBVis, Clinical Graphics, Delft, the Netherlands). The FoB obtains 3D kinematical data using sensors on thorax, scapula, humerus, forearm and thorax. After palpatory identifying three dimensional positions of standard bony landmarks of the arm, shoulder and thorax with respect to the sensors for each patient, local bone coordinate systems are created, based on the subject's individual anatomy. The glenohumeral rotation centre is estimated from the position of five scapular bony landmarks using linear regression [61]. The RoM of the following movements is measured: anteflexion, retroflexion, abduction in frontal plane, internal rotation in 0 and 90 degrees of arm abduction and external rotation in 0 and 90° of arm abduction.

3D kinematics and MRI bony segmentation (3D shape parameters of scapula and humerus) will be combined in custom made computer software (Articulus, Clinical Graphics, Delft, the Netherlands) to reconstruct the subacromial space volume and AH during recorded humerus elevations, allowing dynamic measurements of patient-specific subacromial space characteristics [5,62,63]. Additionally, the effect of a subacromial lidocaïne injection on RoM, scapulohumeral rhythm, reconstructed AH and subacromial volume of the affected shoulder will be analyzed.

*Main kinematic outcome parameters*: Passive and active RoM during standardized arm motions (with and without subacromial anaesthetics) of both arms; Scapulohumeral rhythm of affected and healthy arm; Reconstructed changes in AH and subacromial volume during dynamic arm abduction (combining MRI-based shape parameters and 3D RoM measurements).

#### EMG muscle activation patterns (C, D, G)

We will analyze muscle activation patterns as measured by EMG recordings of 10 shoulder muscles, based on Activation Ratio [58,59] and Principal Action parameters [22,51]. Measurements will be performed before and after a subacromial infiltration of lidocaïne (5 ml, 10 mg/ml), to study potential relations between pain during arm abduction and adductor muscle co-activation and arm-scapula kinematics, respectively.

Subjects are seated with the affected arm in a splint with the upper arm in 45° of internal rotation and the elbow in 90° of flexion. The humerus is positioned in 60° of forward elevation and in 30° of external rotation relative to the transverse plane, Figure 3. The splint is attached to a 3D force transducer which is mounted on a sled so that it can move freely in a direction parallel to the humeral longitudinal axis. The arm is fully supported in order to compensate for gravity. Axial rotation of the humerus is mechanically not restricted to prevent the subjects from generating supplementary moments. In this way, patients can only exert forces perpendicular to the longitudinal axis of the humerus.

**Figure 3 F3:**
[figure not shown]
**Experimental setup for isometric arm-shoulder force tasks in 24 directions**. The subject has the arm in a splint, which is connected to a force transducer. Subjects must bring the arm force driven red cursor into the blue target area, which indicates force direction (n = 24 directions) and force magnitude. The exerted force, perpendicular to the humerus long axis, is recorded together with EMG to measure the activity of 10 individual shoulder muscles.

The subjects are asked to exert a maximal voluntary force (MVF) in 4 equidistant directions with a maximum of 50 N and maintain this force for 2 s using custom made visual feedback software (Matlab, The MathWorks Inc, Natick, MA, USA). The exerted force and force targets are visualized on a display, expressed in cursor that has to be moved to consecutive targets on a wheel in which the spokes denote force directions and the rim denotes the desired force magnitude (Figure 3). Subjects are subsequently asked to exert 75% of the lowest MVF value onto the force transducer for 2 s in each of 24 equidistant directions that are indicated on the display. The same routine of 24 measurements will be performed 30 min after a subacromial injection with lidocaïne. Muscle activations for 10 muscles around the shoulder are recorded in each of the 24 directions during the 2 sets of measurements.

The direction of maximum activity or Principal Action (PA) for each muscle is determined [22,51] and the Activation Ratio of the abductor and adductor muscles similar to the method described above [58,59]. We expect that pain will influence the Principal Action direction of the muscles [51]. Patients with pain will consequently show an increase in activation of the glenohumeral depressors during arm abduction moments (i.e. adductor co-activation as expressed in low Activation Ratio's). The AR's obtained within this 'Principal Action' set-up will be compared to AR's obtained from the derived abduction and adduction tasks as obtained with the EMG set-up applied during the acquirement of radiographs, taking potential experimental dependencies of AR into account.

The second hypothesis is that after lidocaine injection the muscle activation patterns of the patients move toward a normal activation pattern, as expressed in higher adductor Activation Ratio's and near normal Principal Action directions [5,51].

*Main outcome parameters*: Muscle specific Principal Action (PA) parameters and muscle specific Activation Ratios (AR) before and after a subacromial injection with lidocaïne.

#### Model simulation (H)

Impaired cuff function and RoM data obtained from the 3D-Kinematics measurements will be used as input data for the inverse dynamic model simulation with the Delft Shoulder and Elbow Model (DSEM) in order to estimate discrete muscle forces and joint reaction forces with the use of inverse dynamic simulation [64]. Muscle quality and glenohumeral joint stability can be varied and compared to the observations on muscle quality (MRI) and proximal migration (2D radiography) [57].

Similarly to the hypothesized clinical measurements outcomes, we expect to find coactivation of arm adductors on affected shoulders during arm abduction simulations, in combination with altered shoulder muscle force patterns for standardized movements with respect to the control shoulders.

The predicted model muscle forces can be used for validation and interpretation of recorded muscle activations by means of EMG.

#### Patient phenotyping (I)

The radiological and biomechanical outcome measures will be related to patients' clinical status or phenotype. We combine an overall general health outcome measure (i,e, SF36), a regional (e.g. shoulder) outcome measure, and a disease- or condition-specific measure for patient assessment [65].

- SF-36: Questionnaire to measure quality of life, based on physical function, illness, pain and mental health [66].

- Illness Perception Questionnaire (IPQ): measures perception and impact of Illness [67].

- The Disabilities of the Arm, Shoulder and Hand (DASH) score: to quantify impact and functional impairment of shoulder arm and hand function [68].

- Constant Shoulder Score (CS): used by physicians to quantify the severity of symptoms and functional impairment in affected shoulders, compared to the unaffected shoulder [69].

- Western Ontario Rotator Cuff index (WORC): a self-reported outcome measure for assessing shoulder problems as a consequence of rotator cuff disease [70].

- Visual Analogue Scale (VAS) for pain during daily life activities and in rest.

#### Relate outcome measures to pathophysiological mechanisms

Results of the recorded clinical, radiological and biomechanical measurements will be interpreted and combined in order to classify patients in to the hypothesized etiological subgroups (Figure 4). Ultimately, if a patient has evidence of co-activation of arm depressors with abduction but no signs of shape parameters (e.g. acromion classification) playing a role, this would implicate that an intrinsic and dynamic mechanism is the main pathologic mechanism. On the other hand, evidence of e.g. a type III acromion (hooked) without any signs of relative cranial translation of the humerus would be suggestive of a primarily extrinsic and static/structural cause.

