#### Secondary goals

A set of experimental and diagnostic tools is combined to identify structural and biomechanical etiological factors in SIS patients, which will be related to clinical and functional status:

A. Presence and severity of pathologies in the subacromial space with MRI, e.g. (partial) cuff-ruptures, tendinosis, fibrosis or a subacromial inflammatory reaction, and assessment of cuff degradation status.

B. Acromial shape classification and 3D shape parameters of the humerus, scapula and subacromial space volume, using conventional radiographs and segmented MRI-arthrographies.

C. Quantification of cranialisation of the humerus with respect to the scapula at rest and during active arm abduction and adduction tasks with simultaneously acquired shoulder radiographs and Electromyography (EMG) recordings (see D).

D. Measurements of the activation of arm adductors during arm abduction tasks and assessment of the presence of arm adductor co-activation (Activation Ratio).

E. Analyses of 3D-kinematics (arm range of motion and scapulohumeral rhythm) of the affected SIS shoulder compared to the unaffected shoulder and eventual etiologic SIS subgroups, with the use of 3D motion registration.

F. Changes in reconstructed subacromial volume and acromiohumeral distance during arm abduction by combining the recorded 3D-kinematics with the MRI-segmented 3D bony shapes.

G. The effect of a subacromial infiltration of lidocaïne on arm range of motion, scapulohumeral and -thoracic rhythm with arm abduction, reconstructed subacromial volume and muscle activation patterns, including adductor co-activation.

H. Biomechanical analyses of structural or coordinative muscular imbalance by means of model simulation (Delft Shoulder and Elbow Model) with recorded 3D-kinematics as input.

I. Clinical phenotyping, using validated clinical scores and questionnaires.

J. Identification of alternative diagnoses that may cause complaints clinically diagnosed as SIS, using MRI and radiographs (e.g. acromioclavicular-osteoarthritis and subacromial osteophytes, calcifying tendinitis, SLAP lesion or coracoid impingement).

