**Figure 4 F4:**
[figure not shown]
**Schematic outline for relating outcome measures to pathophysiological mechanisms**. We expect to identify one or more of the hypothesized etiological mechanisms in each SIS patient. These mechanisms might be related to the reported variations in SIS symptoms, course, and treatment outcome. (MRI = Magnetic Resonance Imaging, X-ray & EMG task = radiographs during EMG recorded abduction and adduction tasks for measurements of acromiohumeral distance, and FoB = 3D kinematics with Flock of Birds system).

The following scenarios are considered:

1) Dynamically reduced subacromial space, due to (relative) cranial translation of the humerus.

Humerus cranialisation causing encroachment of subacromial tissues will be characterized by limited AH in resting state on standard radiographs, further decrease in AH during abduction tasks, and decreased reconstructed subacromial volume (MRI). In some patients, this cranialisation might be (partially) compensated by I) co-activation of arm adductor muscles, and/or II) altered kinematics of the humerus and the scapula (scapulohumoral rhythm). Nevertheless, instead of a compensation mechanism, altered scapulohumeral rhythm can also be a cause of SIS in some patients (e.g. decreased scapula lateral rotation during arm abduction, with consequent relative cranial translation of the humerus). Pain is suspected to be the main trigger for compensation mechanisms. Therefore, we expect that these compensation mechanisms will be less manifest during the second round of experiments, after a subacromial injection with lidocaine.

Particularly relevant positive outcome measures for this subgroup are: decreased AH, low AR (adductor co-activation), altered Principal Action for adductor muscles, decreased reconstructed subacromial volume during active abduction, degeneration of rotator cuff muscles and altered scapulohumeral rhythm.

2a) Statically reduced subacromial space, due to structural narrowing (classic etiology). The subacromial space can be narrowed as a consequence of structural anatomic variations, e.g. a hooked acromion impinging on the subacromial tissues. These potential causes will be investigated and quantified using shoulder radiographs and (segmented) MRI-arthrographies.

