As a consequence of structures impinging on the rotator cuff, compensation mechanisms might be present to prevent further subacromial encroachment, including altered scapulohumeral rhythm (increased lateral rotation or increased posterior tilt during arm abduction) and adductor co-activation during arm abduction. Again, we expect that these compensations mechanisms will be less manifest after a subacromial injection with lidocaine.

Important outcome measures for this subgroup are: shape parameters of scapula (hooked acromion, Bigliani classification, acromial spurs) and humerus, the presence and extend of rotator cuff tendinosis (fibrosis, tendinitis, partial articular or bursal side tear).

2b) Statically reduced subacromial space, as a consequence of subacromial inflammatory processes, without signs of actual structural subacromial narrowing.

In some subjects, symptoms of SIS are related to predominantly intrinsic causes. In these patients, we expect to find little or no anatomic variations impinging on the cuff and no evidently decreased AH. The hypothesized disbalance between subacromial volume and the space needed for subacromial structures can be caused by e.g. subacromial oedema, fibrosis, tendinosis and tendinitis, which will be mainly assessed by means of MRI.

As a consequence of the subacromial inflammatory reaction and pain, patients might have an altered scapulohumeral rhythm and adductor co-activation.

Main outcome measures for characterizing this subgroup are: the presence and extend of rotator cuff tendinosis (fibrosis, tendinitis, partial articular or bursal side tear) and subacromial oedema.

2c) Statically reduced subacromial space due to encroachment of subacromial tissues by an adjoining pathology or other structures than the acromion.

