#### Statistical analyses

Patient data, including patient characteristics, physical examination, interview, radiological findings, questionnaires, psychological scores, biomechanical measurements and MRI findings will be entered in a database.

With regards to presence of cranial translation of the humerus as detected on radiographs during rest and abduction and adduction tasks, statistical analysis will be performed by a means of repeated measures ANOVA, with the measure of co-contraction controlled as a confounding factor.

For the isometric Principal Action EMG measurements, data are tested by means of a General Linear Model analysis for repeated measures, controlling for factors Muscle, subacromial anaesthetics, sAH and VAS for pain.

RoM in standardized motions will be analyzed with a General Linear Model analysis for repeated measures, controlling for factors VAS pain, subacromial anaesthetic, dAH and sAH. dAH obtained from 3D-kinematics will be analyzed equally.

Additionally, we will use students' unpaired t-tests to compare continuous variables (e.g. patient characteristics, clinical scores, RoM, dAH) between defined pathologic subgroups.

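### The protocol does not settle whether clinical scores help assign patients to subgroups, yet it compares those scores between the subgroups

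*Protocol article*

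**What the plan says.** Two places in the protocol article put clinical data on the input side.

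- **Relate outcome measures to pathophysiological mechanisms**, opening sentence: "Results of the recorded clinical, radiological and biomechanical measurements will be interpreted and combined in order to classify patients" into the hypothesized subgroups.
- **Abstract, Methods**: the list of clinical and experimental methods for identifying intrinsic and extrinsic mechanisms ends with clinical phenotyping, and names the Constant, DASH, WORC and SF-36 scores.

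Three places put clinical data on the outcome side, or leave them out of the classification.

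- **Secondary goals**: the tools are meant to "identify structural and biomechanical etiological factors in SIS patients, which will be related to clinical and functional status".
- **Patient phenotyping (I)**: "The radiological and biomechanical outcome measures will be related to patients' clinical status or phenotype". The instruments are SF-36, IPQ, DASH, Constant Score, WORC and VAS for pain.
- **Scenarios 1 to 2c**: for scenario 1, "Particularly relevant positive outcome measures for this subgroup are: decreased AH, low AR (adductor co-activation), altered Principal Action for adductor muscles", followed by subacromial volume, cuff degeneration and scapulohumeral rhythm. For scenario 2a, "Important outcome measures for this subgroup are: shape parameters of scapula (hooked acromion, Bigliani classification, acromial spurs) and humerus", plus cuff tendinosis. Scenario 2b rests on tendinosis and oedema, mainly by MRI. Scenario 2c rests on MRI and radiographs, with kinematic recordings. No score appears in any list.

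Finally, **Statistical analyses** plans unpaired t-tests to "compare continuous variables (e.g. patient characteristics, clinical scores, RoM, dAH) between defined pathologic subgroups".

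**The concern.** A comparison of clinical scores between subgroups shows whether the mechanisms matter to patients only if the subgroups were formed without those scores. The general sentence on classification and the Abstract let the scores in; the specific sections treat them as something to be explained. As written, whoever combines the results may have the scores at hand.

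Assignment is by interpretation, and the described pictures overlap. Adductor co-activation and altered scapulohumeral rhythm may occur in scenarios 1, 2a and 2b, and tendinosis is listed for both 2a and 2b. Choosing a main mechanism, or the combination group, therefore takes judgement. If symptoms sway that judgement in a consistent direction, subgroups will differ in symptoms even where mechanism and symptoms are unrelated. The secondary aim of relating etiological factors to clinical and functional status would then be partly answered by the way the groups were made.

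**Working it through.** **1. Reading the sections together**

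| Place | Role of clinical data |
|---|---|
| Abstract, Methods | tool for identifying mechanisms; four scores named |
| Relate outcome measures, opening sentence | input to classification; scores not named |
| Secondary goals; Patient phenotyping (I) | variable to which mechanisms are related |
| Scenarios 1 to 2c | absent from the markers |
| Statistical analyses | outcome compared between subgroups |

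The first two rows and the last, taken literally, make the same data both input and outcome. Rows three and four do not. No sentence resolves the difference, and none keeps the scores out of assignment.

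**2. What a leak would do**

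The protocol gives no figure on this point, so this is an illustration. Inputs:

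- Total 100 and one subgroup of 30, from Sample size, where 30 / 0.30 = 100. The rest is 70. Only the split is used; how the 30 was derived does not matter here.
- Two-sided 5% unpaired t-test on one score. The protocol gives p = 0.05; two-sided is assumed.
- Score C, standard normal, unrelated to mechanism.
- Classification index Z = w·C + √(1 − w²)·X, with X independent of C. The 30 highest values of Z form the subgroup.
- w is the correlation between index and score due to leakage. It is **assumed**; nothing in the document gives it. Range shown: 0 to 0.3.

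Expected difference in C between the groups. The cut for the top 30% of a normal variable is 0.524, where the density is 0.3477.

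- Mean of Z above the cut: 0.3477 / 0.30 = 1.159
- Mean of Z below the cut: −0.3477 / 0.70 = −0.497
- Difference in Z: 1.656 SD, so the difference in C is about 1.656·w

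Standard error: √(1/30 + 1/70) = 0.218.

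Rejection rate, normal approximation, with d = 1.656·w / 0.218: Φ(d − 1.96) + Φ(−d − 1.96).

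| w | Difference in C (SD) | d | Formula | Simulation, 10,000 studies |
|---|---|---|---|---|
| 0 | 0 | 0 | 5% | 5.2% |
| 0.1 | 0.17 | 0.76 | 12% | 11.8% |
| 0.2 | 0.33 | 1.52 | 33% | 32.0% |
| 0.3 | 0.50 | 2.28 | 62% | 62.9% |

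A second simulation of 20,000 studies per setting gave 11.9%, 32.5% and 62.9% for w = 0.1, 0.2 and 0.3.

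The model is simpler than the study. It uses one index cut once, where the protocol has four mechanisms and a combination group, and it assumes a leak in one direction. It shows sensitivity to a leak, not that one will occur.

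**The case against.** The strongest reply is that the scores are not in fact an input. The sentence on classification is a general opening. The examples that follow it use co-activation, acromion shape and cranial translation, and the scenario lists are the operative rule. The Figure 4 legend expands only MRI, the radiograph and EMG task, and the kinematic system; the figure itself is not available. The word "clinical" is also loose: Model simulation uses it for outcomes that include adductor co-activation, and it could cover examination findings such as a disturbed scapulohumeral rhythm.

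Much of this stands. A reader might infer that the scores are known to classify patients and that the subgroup comparison is therefore biased. The documents do not support that: no scenario uses a score, and the leak is assumed. But the reply does not remove the ambiguity. The Abstract names four scores among the means of identifying mechanisms, and the classification sentence lists clinical beside biomechanical data, where EMG and kinematics already belong.

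Two further inferences go too far.

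- That this comparison is the only outside check. The Discussion plans a later trial of treatment outcomes by subgroup, and the measurements before and after lidocaine link pain to muscle activation and kinematics within this study.
- That the study's claim about variation in symptoms and scores becomes untestable. The Abstract's Discussion paragraph speaks there of variation reported in the literature, not of what these t-tests will show.

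It is also fair that an article may leave rater blinding and data locking to the full protocol. Their absence is not the point; the conflicting statements about what classifies a patient are.

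**Conclusion.** The point holds as an unresolved conflict in the stated plan. The Abstract and the classification sentence admit clinical measurements as inputs, the goals, phenotyping section and scenarios treat them as what is to be related to mechanism, and the analysis then compares clinical scores between the resulting groups. If scores influence assignment, that comparison is partly circular.

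The size cannot be derived from the document. Under assumed leak correlations of 0.1 to 0.3 and a 30/70 split of 100, the nominal 5% test rejects in about 12% to 63% of studies, with a built-in difference of about 0.17 to 0.5 SD. With no leak it stays near 5%. These figures assume a leak in one direction and no true relation between mechanism and score.

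The primary goal, identifying and classifying mechanisms, is not undermined. What is at risk is the main patient-relevant comparison within the study, and it should be protected. Whether acromiohumeral distance raises a similar problem, being both a subgroup marker and a compared variable, is a separate question.

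**What to change.** Reconcile the passages. In the section relating outcome measures to mechanisms, state that subgroups are assigned only from the radiological, MRI, EMG and kinematic markers listed for scenarios 1 to 2c, without sight of the questionnaire scores, VAS or Constant Score. State also that assignments are fixed before those scores are linked to them. Amend the Abstract's Methods paragraph so that clinical phenotyping is described as what the mechanisms are related to.

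The cost is protocol wording and the order in which data are released; no new data, patients or staff are needed. The downside is small: raters lose clinical context in borderline patients.
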